**Randomization and Dosing**

All patients enrolled in the prevention trial will be randomized to one of the study groups using a permuted block randomization scheme of four. Stratification will be done by Mantoux reading (>5mm and ≤5mm). The group assignment list will be generated centrally before the start of trial and sequentially numbered sealed envelopes containing the study group assigned will be prepared independently. At the initiation of prophylaxis, each patient will be counseled about the importance of taking drugs regularly. Patients will be asked to return the empty packets as well as unused tablets at each monthly visit.

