**Study Design**

The study will be a two-armed prospective randomized clinical trial among HIV- positive patients without active tuberculosis. Enrolled patients will be assigned to one of the two unsupervised self-administered treatment regimens i.e. EH for 6 months or INH alone for 3 years. At the end of a 3-year follow-up, incidence of TB and overall mortality will be compared in each group.

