**Study population and enrollment**

All HIV positive patients seeking care at one of the study centers, above the age of 15 years, not suffering from a serious illness, non-pregnant, and in whom TB was ruled out using the enhanced screening process described in section I, will be approached to participate in the study. The consent form for prophylaxis trial will be read to the patients in the local language and written consent will be obtained from willing patients.

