**Sample Size**

Assuming that prophylaxis will result in reduction of the incidence of TB in HIV positive persons from 7/100 person years (published TRC study) to 3/100 person years, the sample size for each arm is calculated to be 250. Allowing for a 10% drop out rate per year due to death or default, the number of patients required per treatment arm will be 325.

Total number of patients to be admitted to the study: 650

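### A constant block of four, stated in the protocol of a trial with unmasked regimens, makes up to one third of allocations predictable on a list and weakens the sealed-envelope concealment

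*Protocol*

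**What the plan says.** Under Randomization and Dosing, patients are "randomized to one of the study groups using a permuted block randomization scheme of four". The only stratification factor is skin-test result: "Stratification will be done by Mantoux reading (>5mm and ≤5mm". The same section protects the sequence in two ways. The list is drawn up in advance at a central point. The allocations are then concealed, in that "sequentially numbered sealed envelopes containing the study group assigned will be prepared independently". It describes no variation in block size and no step to withhold the size from enrolling staff.

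Study Design describes the arms as "unsupervised self-administered treatment regimens i.e. EH for 6 months or INH alone for 3 years". The numbered regimens under Randomization and Dosing confirm two drugs in one arm and one in the other. Placebo and masking are not mentioned anywhere.

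Study population and enrollment takes in "All HIV positive patients seeking care at one of the study centers", so there is more than one centre. The number of centres is not given, nor whether each holds its own envelope series. Sample Size gives the totals: "the number of patients required per treatment arm will be 325" and, for both arms together, "Total number of patients to be admitted to the study: 650".

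**The concern.** Sealed envelopes hide the next allocation only as far as it cannot be worked out from the earlier ones. Here the stratum is known before randomization, because the Mantoux test is done at month 0. The arm is evident once an envelope is opened. The block length is constant and written down. Anyone who combines these three facts can sometimes name the next arm with certainty.

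This matters because entry is partly a matter of judgement. Under Study population and enrollment, patients must be free of serious illness, which is not defined, and must have had active tuberculosis excluded. Staff may also influence when a patient is enrolled. The arms differ greatly in burden, six months of self-administered drug against three years. Someone who foresees the arm could bring a patient forward or hold one back. Selection of that kind would alter the risk of tuberculosis and death in the arms before treatment begins. Intention-to-treat and log-rank analysis take the arms as formed, so they would carry the selection into the result. The Cox model can adjust only for factors that were measured.

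**Working it through.** **Inputs.** Block size 4, constant (Randomization and Dosing). Two arms (Study Design). Ratio 1:1, which is not stated outright but follows from 325 per arm and 650 in total, since 2 × 325 = 650 (Sample Size). The protocol gives no figure for predictability, so there is none to reproduce.

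**Certain allocations, whole list visible.** A 1:1 block of four has six equally likely orders: AABB, BBAA, ABAB, ABBA, BABA, BAAB. An allocation is certain when one arm is already used up within the block.
- AABB and BBAA: the last two allocations are certain.
- The other four orders: only the last is certain.
- Expected number per block: (2 × 2 + 4 × 1)/6 = 8/6 = 4/3.
- Share: (4/3)/4 = 1/3. Over 650 patients: 650/3 ≈ 217.

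**Best guess, whole list visible.** The recruiter always guesses the arm with more places left in the block.
- First place: 1/2.
- Second place: 2/3.
- Third place: the first two match with probability 1/3, and the guess is then certain. Otherwise it is an even guess: 1/3 × 1 + 2/3 × 1/2 = 2/3.
- Fourth place: 1.
- Mean: (1/2 + 2/3 + 2/3 + 1)/4 = 17/24 = 70.8%, or about 460 of 650, against 50% by chance.

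**One list shared by k equally recruiting centres, each seeing only its own patients.** The third place is certain if the first two match (1/3) and both were the recruiter's own (1/k²). At the fourth place, exactly two of the three earlier allocations are alike, and the recruiter must have seen both (1/k²). The share is (1/3 + 1) × (1/k²)/4 = 1/(3k²).

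| Centres sharing the list | Certain share | Of 650 |
| --- | --- | --- |
| 1, or a separate list per centre | 33.3% | 217 |
| 2 | 8.3% | 54 |
| 3 | 3.7% | 24 |
| 4 | 2.1% | 14 |

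A simulation gave the same shares (33.4%, 8.3%, 3.7%, 2.1%).

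**Alternatives, whole list visible.** Constant blocks were enumerated. Varying blocks were simulated on one long list of 60,000 allocations, with an observer who knows the set of sizes and updates after each allocation.

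| Scheme | Certain share | Best guess right |
| --- | --- | --- |
| Constant 4 (the plan) | 33.3% | 70.8% |
| Constant 6 | 25.0% | 68.3% |
| Constant 8 | 20.0% | 66.6% |
| Random 4 or 6 | about 5% | about 69% |
| Random 4, 6 or 8 | about 2% | about 68% |

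Varying the size removes nearly all the certainty. It does little to the best-guess rate.

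**The case against.** The plan has real safeguards: a central list made in advance, and numbered, sealed, independently prepared envelopes. Even a recruiter who tracks everything remains uncertain about two thirds of allocations. The one-third figure also needs conditions that the protocol does not establish, namely that the person judging eligibility knows the block size and sees every earlier allocation in that stratum of the list. The order of events helps too. Under Enrollment and baseline investigations, consent comes before laboratory testing, and numeric laboratory and CD4 limits apply before entry. Both arms receive active preventive therapy, and the protocol gives no reason to expect steering in a particular direction.

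All of this stands, and it limits the point without removing it. The block size appears in the protocol with nothing to keep it from enrolling staff, and some entry criteria remain matters of judgement. The text does not say that an envelope is opened only after eligibility is on record.

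Two stronger readings are tempting. A reader might infer that the fixed block defeats the envelopes. The two thirds that stay uncertain show that it does not. A reader might also infer that one numbered series cannot be used in order across several centres. The documents do not support this: they do not say where the envelopes are held, a central holder could release them in order, and a list can be divided at multiples of four without breaking a block.

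**Conclusion.** The point holds as a weakness in a stated design rule. A constant block of four with unmasked regimens allows up to one third of allocations, at most about 217 of 650, to be known in advance, with a best-guess rate of 71%.

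That is an upper bound. It assumes 1:1 allocation, knowledge of the block size, and sight of every earlier allocation on the list. It applies if each centre has its own list, or if one list is divided into whole blocks. If centres share a list and see only their own patients, the certain share drops to about 8%, 4% or 2% with two, three or four equally recruiting centres. The protocol does not settle which arrangement applies.

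That the trial is open-label is inferred from the regimens; the protocol does not use the term. Nothing in the document shows that any allocation was or will be foreseen, and the direction of any resulting bias cannot be stated. The change is still worth making, because it is nearly free and selection at entry cannot be undone by the analysis.

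**What to change.** Before the start:
- Regenerate the list with randomly varying block sizes, for example 4, 6 and 8, within Mantoux stratum. If envelopes are held at the centres, make a separate list for each centre. Separate lists alone could increase what a centre sees of its own sequence, so they should come only together with varying sizes.
- Keep the block sizes out of the protocol held by enrolling staff.
- State who holds the envelopes, and that each is opened only after eligibility and consent are recorded. Mark the envelope with a study number and not the patient's name, in keeping with the confidentiality commitment under Ethical Issues.

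Certain allocations then fall from 33% to about 2%, or to about 5% with sizes 4 and 6 only, even for an observer who knows the set of sizes. The best-guess rate falls only from 71% to about 68%, so the procedural steps still matter.

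The cost is regenerating one list, with no extra staff. Balance is slightly looser. Within a block of four the arms can differ by at most 2 patients at any moment, and within a block of eight by at most 4. A difference of a few patients per stratum is therefore possible, and it can add up across lists if each centre has its own.

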Despite their increased susceptibility to TB, patients with HIV/AIDS can be cured of TB by Directly Observed Therapy, Short-Course (DOTS). DOTS is a technical and management package aimed at diagnosing and curing as many infectious tuberculosis cases as possible with the twin goals of >85% cure rate and 70% case-finding. If effectively implemented, this strategy should cut the chain of transmission in the community by curing most of the infectious cases. The Revised National Tuberculosis Control Program (RNTCP) utilizes the five components of DOTS and is being implemented in India in a phased manner from 1993 onwards.To date, a population of 250 million has been covered and the entire country is expected to be covered by 2004. Recognizing the serious threat posed by TB/ HIV co-infection, the RNTCP calls for strengthening collaboration between TB and AIDS control programs for better management of HIV-infected patients with TB. However, to date, there are no specific technical guidelines for diagnosis, treatment or prevention of TB among HIV infected persons.

Diagnosis of tuberculosis among HIV-infected persons is often delayed and difficult to make, as HIV-infected persons with TB are more likely to have negative sputum smears and minor and non-specific x-ray abnormalities. Among HIV-infected persons with an intact immune system, the clinical presentation is similar to that among HIV negative individuals. However, the pathogenesis and clinical features of TB change markedly among HIV positive persons with immunodeficiency (e.g CD4 counts of < 200). Studies comparing the proportion of sputum smear positive patients among HIV infected and non-infected tuberculosis patients have found a lower proportion of sputum smear positive patients among those with HIV infection compared with HIV negative patients. Recently, a diagnostic algorithm using the response to a course of broad - spectrum antibiotics has been used in an attempt to improve the specificity of diagnosis of smear-negative tuberculosis and this approach has been incorporated into the RNTCP also.

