**Enrollment and baseline investigations**

All patients who provide a written consent to participate in the trial will be interviewed by a social worker using a standard questionnaire. Patients with previous history of TB treatment of greater than 1 month or those on anti-retroviral drugs will be excluded from the study. Blood samples will be collected from patients meeting initial eligibility criteria to test for laboratory eligibility criteria. Standardized laboratory investigations will include complete heamogram (total and differential leucocyte counts, platelet counts and haemoglobin estimation), Renal function test (serum uric acid, blood urea, serum creatinine), Liver function tests, random blood sugar (BS), urine albumin and urine sugar. Patients who fulfill laboratory criteria (hemoglobin =>70 g/L, granulocyte count >1.1 X 109/L, platelet count > 100X 109/L, serum alanine amino transferase concentration <2.5 times the upper limit of normal, and serum creatinine concentration <1.1 mg%, random blood sugar < 140 mg%) will be enrolled in to the study.

Patients whose CD4+ cell count is below 100 absolute count or 10% of the total leucocyte count will not be admitted to the study, as they may have a latent focus of tuberculosis, which cannot be diagnosed by standard techniques available.

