**Statistical analysis and outcome measures**

The primary end point of the study will be development of tuberculosis and the secondary endpoints will include adverse drug reactions and mortality rate. The intention-to-treat approach will be used for analyzing the data for primary and secondary end points. Annual interim analyses will be done to ensure timely identification of any significant risks or benefits to patients. The treatment groups will be compared to note random distribution of baseline demographic and socio-economic, clinical and laboratory characteristics. The incidence of tuberculosis will be estimated by the person-year method. Cumulative proportion will be used for adverse reactions and mortality. The log rank test of significance will be used to compare cumulative incidence of TB in the treatment groups. Survival analyses using the log rank testing the null hypothesis and Kaplan Meier curves for depicting cumulative survival in TB and mortality will be done to compare outcomes between study groups. Multivariate analyses will be performed using Cox’s proportional Hazards model.

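### Baseline CD4, known before admission, is left out of the log-rank comparison, as is the Mantoux stratum: a small loss of efficiency that costs almost nothing to recover

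*Protocol*

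**What the plan says.** **Allocation.** Protocol, Randomization and Dosing: permuted blocks of four, with one stratification factor: "Stratification will be done by Mantoux reading (>5mm and ≤5mm".

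**CD4 at entry.** Protocol, Enrollment and baseline investigations: patients with CD4 below 100, or below 10%, are not admitted, "as they may have a latent focus of tuberculosis, which cannot be diagnosed by standard techniques available". The result must therefore be in hand before allocation. The Investigation and follow up table also lists CD4 at month 0. Patients on antiretroviral drugs are excluded.

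**Relevance of CD4.** Protocol, Introduction: "the pathogenesis and clinical features of TB change markedly among HIV positive persons with immunodeficiency (e.g CD4 counts of < 200". The band from 100 to 199 is not barred by the absolute-count floor.

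**Analysis.** Protocol, Statistical analysis and outcome measures: the log-rank test compares TB incidence between groups, with no strata named. Mortality is compared by the same methods. On baseline data: "The treatment groups will be compared to note random distribution of baseline demographic and socio-economic, clinical and laboratory characteristics". Multivariate Cox analyses are planned; their covariates are not listed, and they are not linked to the primary comparison.

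**The concern.** A baseline value that is already collected, and that probably predicts both outcomes in the study objective, is used neither to balance the arms nor in the named test. Two things follow. A chance excess of low-CD4 patients in one arm would push the TB and mortality contrasts in the same direction. A log-rank test that ignores a strong prognostic factor is also somewhat less sensitive. Comparing baseline characteristics can reveal an imbalance, but it does not allow for it. The same test also omits Mantoux, the one factor on which allocation is stratified.

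**Working it through.** **Inputs from the protocol (Sample Size; Follow-up)**
- TB incidence "from 7/100 person years (published TRC study) to 3/100 person years", so the planned hazard ratio is 3/7 = 0.43.
- "the sample size for each arm is calculated to be 250", then "Allowing for a 10% drop out rate per year due to death or default". 250 × 1.30 = 325 per arm, 650 in total.
- Three years of follow-up from admission.

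**Assumptions, because the protocol gives no figure.** The share of entrants with CD4 below 200 is p = 30–50%, and their TB hazard relative to the rest is h = 2–4. Tests are two-sided at 5%.

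**1. The plan's own figure.** Three-year risks are 1 − exp(−0.21) = 18.9% and 1 − exp(−0.09) = 8.6%. Comparing two proportions at 90% power gives 232 per arm, or 251 with continuity correction, against the stated 250. Alpha, power and horizon are not stated, so this match is not unique: two-year risks at 80% power without correction give 255.

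**2. Chance imbalance at 325 per arm.** SD of the between-arm difference in the low-CD4 share = √(2p(1 − p)/325). With d = 1.96 SD and no true treatment effect, the rate ratio becomes [1 + (h − 1)(p + d/2)] / [1 + (h − 1)(p − d/2)].

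| p | SD (points) | d (points) | ratio, h = 2 | h = 3 | h = 4 |
|---|---|---|---|---|---|
| 0.3 | 3.6 | 7.0 | 1.056 | 1.092 | 1.118 |
| 0.4 | 3.8 | 7.5 | 1.055 | 1.087 | 1.108 |
| 0.5 | 3.9 | 7.7 | 1.053 | 1.080 | 1.097 |

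Example (p = 0.4, h = 3): (1 + 2 × 0.4377)/(1 + 2 × 0.3623) = 1.875/1.725 = 1.087. A gap above 5 points has a 16–20% chance; one above 10 points, about 1%.

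**3. That shift against sampling error.** Loss of 10% per year is a hazard of δ = −ln 0.9 = 0.105. Expected events = 325 × Σ λ/(λ + δ) × [1 − exp(−3(λ + δ))], with λ = 0.07 and 0.03: 325 × (0.1633 + 0.0740) = 77. The SE of the log hazard ratio is about 2/√77 = 0.23. The largest shift, ln 1.118 = 0.11, is about half of one SE.

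**4. Power.** Simulation: 650 patients, three years, exponential TB times, 10% yearly loss, blocks of four, p = 0.4, 10,000 trials per setting. Power in %, with two decimals kept so that differences can be followed:

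| True HR | h | Plan as written | Test stratified by CD4 | Allocation only | Both |
|---|---|---|---|---|---|
| 3/7 | 2 | 94.77 | 95.04 | 94.64 | 94.80 |
| 3/7 | 3 | 93.65 | 94.61 | 94.45 | 94.85 |
| 3/7 | 4 | 93.23 | 94.61 | 94.00 | 94.86 |
| 0.60 | 2 | 63.59 | 64.07 | 63.83 | 64.42 |
| 0.60 | 3 | 62.95 | 64.78 | 62.25 | 63.91 |
| 0.60 | 4 | 60.40 | 63.87 | 60.16 | 63.00 |

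At 3/7 the gain is 0.3–1.4 points from the test alone and 0.0–1.6 from both. At 0.60 it is 0.5–3.5 and 0.8–2.6. Changing the test alone therefore recovers essentially all of the loss. The simulation standard error is about 0.2 points near 95% and 0.5 near 63%.

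**5. Type I error, same setting.** Plan as written: 4.7–5.1%. Test stratified: 4.9–5.1%. Allocation stratified by CD4 but plain test: 4.4–4.6% at h = 2 and 3, and 3.9% at h = 4, which is conservative. Both: 4.6–5.0%.

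**Limits.** Mantoux strata were not modelled. CD4 entered as two bands, so the value of log CD4 in a Cox model was not simulated.

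**The case against.** The strongest reply is that this is a refinement and corrects no error. Randomisation already covers chance imbalance within the 5% error rate, and the worst shift above is half of one SE. At the planned effect, power is 93–95% either way. Mantoux was a reasoned choice of stratum, since the Introduction treats efficacy in Mantoux-negative persons as an open question. Cox covariates are commonly left to a statistical analysis plan, and the one for this trial, which is not shown, may already include CD4.

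Most of this stands, and it limits the point to efficiency. What remains is that the protocol names a log-rank comparison with no strata and does not tie the Cox model to it. A better-specified test is available from data already collected. Overall error control also does not describe a trial that has drawn an edge-of-range imbalance. In a simulation with no true difference (325 per arm, three years, an average of 5–7 TB cases per 100 person-years), the plain test's false-positive rate given such an imbalance was about 5–8%.

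A reader might infer three stronger things that the documents do not support:
- *That the protocol expects undetected TB in the 100–199 band.* The latent-focus reason is given only for the excluded range. The remark about counts below 200 concerns pathogenesis and clinical features, not incidence. Prognostic value among admitted patients is a plausible inference.
- *That the analysis makes no provision for adjustment.* A multivariate Cox model is planned.
- *That stratifying allocation by CD4 is the main remedy.* On its own it adds little power and makes the plain test conservative.

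**Conclusion.** The point holds as a free improvement. The primary comparison omits both baseline CD4 and the Mantoux stratum, and the cost is small: about 0–1.6 points of power at the planned hazard ratio and about 0.5–3.5 points at 0.60, with overall type I error intact. An imbalance at the edge of its 95% range would shift the TB rate ratio by about 5–12%.

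The 0.60 case deserves some weight. Sample Size attributes the fall from 7 to 3 per 100 person-years to prophylaxis, but both arms receive prophylaxis, so the true difference between regimens may be smaller than planned.

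All these sizes rest on the assumed low-CD4 share and CD4 effect, neither of which is in the protocol. The power figures use a 40% share only.

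**What to change.** In Statistical analysis and outcome measures, make the primary TB comparison and the mortality comparison log-rank tests stratified by Mantoux (the allocation stratum) and baseline CD4 (below 200 v 200 or more). Take the treatment hazard ratio from a Cox model that includes the Mantoux stratum and log baseline CD4 as pre-specified covariates. Use the month 0 CD4 only, because later values could be affected by what happens after allocation. If the statistical analysis plan already says this, align the protocol wording with it.

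Adding CD4 to the allocation strata, giving four in all, is optional and only sensible if the lists have not been issued. If it is done, the test must be stratified by CD4 as well.

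The cost is slightly more analysis work, with no new test, visit or patient. Changing the allocation would also need extra lists and envelope sets (possibly at each centre) and leave a few incomplete blocks.
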